Lower-risk MDS anemia, also known as ineffective hematopoiesis, is primarily caused by the excessive proliferation of red blood cell precursors, which fail to mature and impair the ability of red blood cells to carry oxygen in the blood. Additionally, erythropoiesis and iron homeostasis are closely related. Abnormal iron metabolism is an independent risk factor affecting the prognosis of patients with lower-risk MDS [2], and hepcidin plays a key role in iron homeostasis. MDS has a complex iron regulation mechanism: anemia, hypoxia, inflammation, and iron overload, which have opposite effects on hepcidin production. Compared with healthy individuals, patients with MDS deprived of blood transfusion have significantly increased serum ferritin (SF) and hepcidin levels, but have decreased hepcidin/SF ratio [4, 5]. In patients with lower-risk MDS undergoing blood transfusion, the hepcidin levels initially increase; however, as the amount of transfused blood increases, the hepcidin levels gradually decrease, eventually causing iron overload [6]. Iron overload would further aggravate the underlying hematopoiesis deficiency in those with MDS, making blood transfusion ineffective [2].

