### Data collection

Most patients in the outpatient clinic would be enrolled in the study. We would first obtain the patient’s informed consent. Then, we will collect the patient’s demographic data (sex, age, occupation, home address, diagnosis, and past history of illness) and help the patient fill out the TCM symptom scale to determine the type of symptom presented. A peripheral blood sample would be collected from each included patient prior to the initiation of treatment. The blood sample would be examined for various biochemical parameters such as liver and kidney function, iron metabolism-related indicators, hepcidin levels, and inflammatory factor-related markers. By randomly assigning them into either group, the patients would be administered with oral doses of conventional medicine with YGS or placebo for 3 months (12 weeks). At 1-, 2-, and 3-month intervals, the patients will be followed up in order to determine who among them would be suitable to fill up a new TCM symptom scale form to rate their symptoms, and a fresh peripheral blood samples would be collected (Table 2). Use case record form to collect patient clinical data and test data, and enter the information and data into electronic data capture.

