### Efficacy assessment

#### Primary outcome

The primary outcome is the blood hemoglobin level; by comparing it to the baseline level prior to the initiation of treatment, an increase of 10 g/L is considered as an effective treatment outcome.

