#### Secondary outcomes

The secondary outcomes measure the changes in TCM symptom scores, iron metabolism, hepcidin levels, and inflammatory factors. Spleen *Qi* deficiency syndrome is primarily characterized by poor appetite, fatigue, abdominal distension after meal or in the afternoon, and abnormal stool. The effectiveness of TCM is evaluated using the TCM syndrome score method (Table 3). According to the Standard Criteria for Syndrome Differentiation by TCM [11], a reduction in TCM syndrome score by ≥30% indicates that the clinical symptoms of spleen *Qi* deficiency either improved or disappeared and the treatment is considered clinically effective. The TCM syndrome score is calculated as follows: [(scores before treatment − scores after treatment) ÷ scores before treatment] × 100%. The indicators for iron metabolism are serum iron, total iron-binding capacity, SF, and soluble transferrin receptor. Inflammatory factors include interleukin (IL)-1, IL-6, and tumor necrosis factor (TNF)-α.

**Table 3 Tab3:** TCM syndrome scores for spleen *Qi* deficiency

Symptom	Score		
	Mild = 2	Moderate = 4	Severe = 6
Reduced food intake	No appetite, but maintain the original intake	Intake volume reduced by 1/3 compared before the onset of symptoms	Intake volume reduced by 2/3 compared before the onset of symptoms
Fatigue	Slightly tired and inactive but able to perform basic daily activities	Obvious sign of burnout, barely performing daily activities	Systemic weakness of the limbs, unable to perform daily activities
Bloating after meal	Slight abdominal distension, which can disappear within half an hour; is not severe; and does not require medications	Slight abdominal distension, which can disappear within mild; is not severe; and does not require medications	Abdominal distension cannot be improved within 2 h, affecting life, or taking ineffective medicines
Abnormal stool	Soft stools or slightly watery stools, piles are not formed, frequency of bowel movements: 2–3 times/day	Watery stools, loose stools, frequency of bowel movements: 4–5 times/day or 1–2 times/day	Loose stools, more than 3 times/day
Reduced talkativeness/responsiveness	Low energy, not interested to talk or respond	Mental fatigue, sleepy, not interested to engage in conversation	Extremely fatigued, idle
Absence of taste/ thirst	Occasional tasteless	Sometimes tasteless, reduced water intake	Persistent absence of taste, not thirsty all day long

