### Statistical analyses

A descriptive statistical analysis of all the quantified variables in this study would be performed. The mean, median, and standard deviation will be calculated for quantitative variables, while the absolute and relative frequencies will be calculated for qualitative variables. The SPSS software (version 25.0; IBM Inc., USA) would be used for data processing and analysis. Statistical analysis would be based on the intention-to-treat and per-protocol population principles. The missing data can be processed using the last observation carried forward method. To compare the changes in TCM symptom scores and hematological data of patients before and after taking intervention treatment, multiple comparisons would be performed. A repeat measurement data analysis of variance will be initially conducted followed by a separate effect analysis, including comparisons between groups at each time point, using a multivariate logistic regression model to analyze the correlation between iron metabolism, hepcidin levels, and IL-6, TNF-α, IL-1 expression changes, and curative effect. Additionally, a subgroup analysis can be performed according to the R-IPI, and covariance analysis can be performed considering the factors such as age and sex. A two-sided *P* value of < 0.05 is considered significant.

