YGS is an oral concoction first reported in the Pediatric Medicine Card Straight Tactic, a famous classical book of TCM written approximately 900 years ago. YGS is known for its functions of tonifying the splenic *Qi* and gasification stagnation. YGS has been traditionally used in Korea to treat a variety of inflammatory diseases; pretreatment with YGS inhibited the production of TNF-α훼 and IL-6 in LPS-stimulated mouse peritoneal macrophages [16], which is consistent with our previous animal experiment results [7], indicating the confirmed inhibitory effect of YGS on inflammatory factors. In our current study, we intend to enroll patients with MDS anemia who are not dependent on blood transfusion and provide them with relevant treatments during the early stages of lower-risk MDS. In patients with lower-risk MDS, early T cell function is increased, and inflammatory factors are highly expressed [17], which is the same as the pathological process of iron metabolism in ACD. Therefore, based on a previous study, we hypothesized that YGS can regulate iron metabolism by reducing the inflammatory factors of lower-risk MDS, thereby improving anemia. We intend to include 60 patients with lower-risk MDS anemia; conduct a randomized, double-blind, placebo-controlled parallel trial; administer oral YGS granules or placebo granules to included patients; and evaluate the clinical efficacy of this treatment.

This trial has the following advantages: (1) This study is a randomized, double-blind, placebo-controlled, multicenter study that is scientific and rigorous. (2) At present, no relevant research has evaluated the effects of TCM on inflammatory factors and iron metabolism in MDS. The findings of this study would fill this gap of knowledge in the literature. This study has certain limitations. It only evaluates the early stages of MDS; most of the patients with MDS are already on the late stages when they see a doctor. Therefore, it might be difficult to recruit patients, and we have to set the sample size based on the minimum number of cases required for statistical analyses. In this study, MDS treatment using Western medicine is also recorded as an individualized treatment regimen, which would be further analyzed as a stratified group of results in our statistical analyses.

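### The logistic regression of curative effect on marker changes pools both randomised arms without listing treatment arm, so its marker association mixes the between-arm shift with the within-arm link

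*Protocol article*

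**What the plan says.** The Statistical analyses section starts with a repeated-measures analysis of variance, "followed by a separate effect analysis, including comparisons between groups at each time point". The same sentence then plans a further model, "using a multivariate logistic regression model to analyze the correlation between iron metabolism, hepcidin levels", continuing with "IL-6, TNF-α, IL-1 expression changes, and curative effect". The listed ingredients are marker changes and a response; treatment arm is not named, and no time window is given.

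For the markers, the Secondary outcomes section says "The indicators for iron metabolism are serum iron, total iron-binding capacity, SF, and soluble transferrin receptor". With hepcidin and three cytokines that makes eight. Curative effect is not defined in that sentence. The Primary outcome section offers the obvious binary candidate: "an increase of 10 g/L is considered as an effective treatment outcome". On timing, the Data collection section says "At 1-, 2-, and 3-month intervals, the patients will be followed up", with blood drawn each time.

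The Discussion gives the biological rationale: "we hypothesized that YGS can regulate iron metabolism by reducing the inflammatory factors of lower-risk MDS, thereby improving anemia".

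**The concern.** The model is fitted to two groups that were randomised to different treatments. If YGS raises hemoglobin and also shifts a marker by an unrelated route, YGS patients will tend to have both the response and the shifted marker, and placebo patients neither. A model without arm reads that contrast as a marker-response association even if the two are unrelated within either arm. The reverse can also happen: a genuine within-arm link may be hidden when the arm shift points the other way.

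This is the only described analysis that joins the markers to response, so a reader is likely to set its result beside the pathway proposed in the Discussion. At stake is the interpretation of a secondary analysis. The primary hemoglobin comparison and the randomised marker comparisons are unaffected.

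**Working it through.** **The plan's own figure.** The article gives no figure for the regression, so the sample size supplies the inputs. With hemoglobin rises of 20 and 14 g/L, SD 7, two-sided alpha 0.05 and 80% power:

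n per group = 2 × [(1.96 + 0.84) × 7 / 6]² = 21.3, rounded up to 22, as stated.

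The printed symbols σ = 14 and δ = 7 would give 63, so SD 7 and difference 6 are used as the main case and SD 14 as a variant.

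**Response rates implied (SD 7, rise of at least 10 g/L).**
- Control: Φ((14 − 10)/7) = 0.72
- YGS: Φ((20 − 10)/7) = 0.92
- Expected non-responders among 60: 30 × (0.284 + 0.077) = 10.8, about 11

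**Why pooling creates a link.** With 1:1 allocation, marker change in SD units with arm shift m, hemoglobin shift h = 6/7 = 0.857 SD, and within-arm correlation r:

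pooled correlation = (r + 0.25·m·h) / √[(1 + 0.25·m²)(1 + 0.25·h²)]

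- r = 0, m = 1: 0.214 / √(1.25 × 1.184) = 0.18
- r = 0, m = 0.5 and 1.5: 0.10 and 0.24
- r = 0, m = 1, SD 14 (h = 6/14 = 0.429): 0.107 / √(1.25 × 1.046) = 0.09
- r = 0.4, m = −1, SD 7: (0.4 − 0.214) / 1.216 = 0.15, so most of a real link disappears

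**Simulation.** 2,000 trials per scenario, hemoglobin rise of at least 10 g/L regressed on one marker change, likelihood-ratio test at 0.05. The marker shifts and correlations are assumptions; the documents give none. The table has SD 7, a hemoglobin effect of 6 g/L and no within-arm link.

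| Marker shift (SD) | Without arm, 30/arm | With arm, 30/arm | Randomised marker comparison, 30/arm | Without arm, 22/arm | With arm, 22/arm |
|---|---|---|---|---|---|
| 0.5 | 8% | 6% | 48% | 7% | 5% |
| 1.0 | 16% | 6% | 97% | 12% | 6% |
| 1.5 | 26% | 5% | 100% | 21% | 6% |

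Across all simulations of this kind, the with-arm rate ran from about 5% up to 9%. At SD 14, with shifts of 0.8 to 1.2 SD, the rate without arm is about 8% to 10%. For masking (r = 0.4, opposing shift of about 1 SD), the link is found in about 11% of trials without arm and 55% with it.

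**What the arm term does not change (30/arm).**

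| Scenario | Without arm | With arm | Randomised marker comparison |
|---|---|---|---|
| No link and no effect | 6% | 6% | 5% |
| YGS inert, r = 0.2 | 24% | 25% | 5% |
| YGS inert, r = 0.4 | 66% | 65% | 5% |
| YGS inert, r = 0.6 | 97% | 97% | 5% |
| YGS raises Hb by 6 g/L, marker not shifted, r = 0.4 | 52% | 56% | 6% |

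**The case against.** The case against is substantial, and much of it stands.

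**Inert YGS.** A reader might infer that the missing arm term is why an inert YGS yields a significant link. It is not: the rates are the same with and without arm. They are also not error rates. The simulation builds in a real within-patient correlation, and a correlation analysis detects it.

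**Mechanism.** A reader might infer that the plan presents this regression as a test of mechanism, or as the only analysis bearing on the Discussion's hypothesis. The documents support neither. The article calls the analysis a correlation and does not tie it to the hypothesis. The markers are secondary outcomes with planned between-group comparisons, which address whether YGS changes inflammation and iron metabolism.

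**Biology.** The Background lists "anemia, hypoxia, inflammation, and iron overload, which have opposite effects on hepcidin production". That makes marker changes plausible when hemoglobin changes. It does not show that every patient whose hemoglobin rises will show them, and it says nothing about hemoglobin altering the cytokines.

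**Condensed text.** The article does not exclude an arm term, and it gives no window for the changes. A fuller plan may settle both, so same-period change is only the natural reading and is not a finding here. The arm point survives in a limited form: the article does list the variables of the model, and arm is not one of them. If a fuller plan includes arm, only the wording needs aligning.

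**Size.** The distortion needs a real YGS effect on both hemoglobin and the marker. At a 0.5 SD shift it is slight (8% against 6%). The simulated model has one marker; the planned model has several.

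**Conclusion.** The point holds as a modest, inexpensive improvement to a secondary analysis. As described, the regression pools two randomised arms without arm among its terms, so its marker association is not a clean within-arm association whenever YGS shifts both hemoglobin and a marker. With a 6 g/L effect, SD 7, 30 per arm and no within-arm link, assumed marker shifts of 0.5 to 1.5 SD produce a significant link in roughly 8% to 26% of trials, against about 5% to 9% with arm. At SD 14 the excess is small. A real link can be hidden when the shift opposes it.

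These sizes rest on assumed shifts and correlations, on a single-marker model, and on reading curative effect as the 10 g/L response. With or without arm, the regression supports association only and cannot by itself establish the pathway.

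**What to change.** In the Statistical analyses section, name treatment arm as a term in whatever form of the logistic model is kept, and report each marker association adjusted for arm. Add one sentence saying that any claim that YGS changes inflammation or iron metabolism rests on the planned randomised between-arm comparison of the markers, and that the regression describes association.

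As an optional sensitivity analysis, relate the month-1 marker change to month-3 hemoglobin, using blood samples already scheduled. This was not simulated. It does not guarantee that cause precedes effect, because hemoglobin may also move in the first month.

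No new data or visits are needed. The cost is one more parameter and slightly wider intervals. With about 11 non-responders expected among 60 patients and eight markers, that parameter is a reason to keep the rest of the model small, not a reason to leave arm out.

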### Randomization and double-blind approach

Participants who met the inclusion criteria and signed an informed consent form would be allocated to a group (Fig. 1). Based on a stratified block randomization design with a 1:1 ratio, two groups of patients would be assigned by the study center at the time of study. Allocation of patients is based on the random numbers (1 to 60) generated using an SPSS software version 25.0, and patient’s details are saved and kept in a sealed envelope by an independent clinical statistician based on the double-blind research method. In the study, the procedures of generating random numbers, evaluating the results of primary and secondary outcomes, and statistical analysis are independently performed by dedicated personnel who are blinded to outcome data. Upon completion of the study and data analysis, the efficacy and safety of YGS treatment shall be evaluated. During the clinical trial period, the treatment regimen of both study groups would be managed by their respective study center/hospital according to the approved treatment plan. If a patient develops a serious adverse reaction or life-threatening condition during the course of clinical trial, the clinician responsible for the patient must provide the best on-site medical care. Simultaneously, the clinician must immediately report the incidence to the inspector, upon which the letter containing patient’s treatment grouping information needs to be opened to break the blind, and the type of drug used is identified to ensure that the patient is provided with the appropriate emergency medical assistance. Once a blind is uncovered, the case would be regarded as a shedding case and would be excluded from the statistics, and any occurrence of adverse reactions would be recorded.

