### Sample size considerations

Based on the sample size estimation formula (*n*1= *n*2 =2×[(μα+μβ)σ/δ]^2^+ μα^2^), the main research outcome indicator is the change in hemoglobin (Hb) levels, which will be used to estimate the sample size; compared with the baseline results, the Hb level of the experimental group (conventional medicine + YGS) increased to 20 g/L, while the Hb level of the control group (conventional medicine + placebo) increased to 14 g/L (standard deviation: 7 g/L, *n*1=group 1, *n*2= group 2, σ=14, δ=7, bilateral α=0.05, μα=1.96, unilateral β=0.2, μβ=0.84); therefore, each group should comprise 22 patients; considering a 30% loss due to follow-up, each group should comprise 30 patients. Therefore, we intend to recruit 60 patients from March 2020 to December 2021.

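### The main Hb analysis includes neither baseline Hb as a covariate nor the apparent randomisation stratum, which costs precision but not validity

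*Protocol article*

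**What the plan says.** All places are in the protocol article.

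- **Statistical analyses.** The Hb data go into a repeated-measures ANOVA, followed by group contrasts visit by visit. No covariate is named for either step. Adjustment is mentioned once, as a possibility: "covariance analysis can be performed considering the factors such as age and sex".
- **Randomization and double-blind approach.** "Based on a stratified block randomization design with a 1:1 ratio, two groups of patients would be assigned by the study center". The section on setting and participants gives three hospitals.
- **Data collection.** "A peripheral blood sample would be collected from each included patient prior to the initiation of treatment". A baseline Hb must exist for every patient, because eligibility requires Hb below 110 g/L and the primary outcome is judged against baseline.
- **Primary outcome and Sample size considerations.** The outcome is Hb relative to baseline, and the sample size is built on the change in Hb.

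**The concern.** Two variables known before treatment have a natural place in the primary model. Baseline Hb is likely to be correlated with later Hb. The factor used to stratify randomisation should appear in the analysis because balancing on it changes the true sampling variance of the treatment difference. The plan requires neither, and leaves covariance analysis optional with an open list of examples.

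The two omissions have different consequences. Without baseline as a covariate, the change-score comparison is correctly calibrated but usually has a larger variance than it needs. Without a stratum that predicts the outcome, between-stratum variation stays in the residual although randomisation has already balanced it, so the reported standard error exceeds the true one. The Discussion says recruitment may be difficult and that the sample size was set at the minimum needed for analysis, so precision that costs nothing is worth having.

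**Working it through.** **Inputs from Sample size considerations.** "bilateral α=0.05, μα=1.96, unilateral β=0.2, μβ=0.84"; "the Hb level of the experimental group (conventional medicine + YGS) increased to 20 g/L"; "the Hb level of the control group (conventional medicine + placebo) increased to 14 g/L"; "standard deviation: 7 g/L". The implied difference is 20 − 14 = 6 g/L.

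**The plan's own figure.** 2 × [(1.96 + 0.84) × 7/6]² = 21.3, rounded up to the stated 22 per group. The printed formula with its added 1.96² gives 25.2, and the printed symbols ("σ=14, δ=7") give 66.6. That conflict is a separate matter. I use SD 7 and difference 6 because they reproduce 22. The relative gains below do not depend on this choice.

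**Patients per arm.** 30 less the planned 30% loss is 30 × 0.7 = 21.

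**Baseline Hb as covariate.** Let ρ be the baseline-to-follow-up correlation and k the ratio of follow-up SD to baseline SD. Neither is in the documents.

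- Variance of change ∝ 1 + k² − 2ρk
- Variance after baseline adjustment ∝ k²(1 − ρ²)
- The first minus the second is (1 − ρk)², which is never negative. Adjustment therefore cannot lose, apart from degrees of freedom.
- With k = 1 the ratio of adjusted to change-score variance is (1 + ρ)/2.

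Power below is for a two-sided 5% t-test at 21 per arm, with difference 6 and k = 1. The unadjusted figure with SD 7 is 77%.

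| ρ (assumed) | Variance ratio | Residual SD | Fall in SE | Power |
|---|---|---|---|---|
| 0.4 | 0.70 | 5.86 | 16% | 90% |
| 0.5 | 0.75 | 6.06 | 13% | 88% |
| 0.7 | 0.85 | 6.45 | 8% | 84% |
| 0.9 | 0.95 | 6.82 | 3% | 79% |

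Taking three degrees of freedom away changes these powers by less than 0.2 percentage points.

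**Unequal variances.** Eligibility truncates baseline Hb at 110 g/L and does not truncate follow-up, so k may exceed 1. With k = 1.3 (assumed):

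- ρ = 0.4: 1.69 × 0.84 / (2.69 − 1.04) = 0.86
- ρ = 0.7: 1.69 × 0.51 / (2.69 − 1.82) = 0.99

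At ρ = 0.7 the variance gain is then about 1%, and power at 21 per arm goes from 77% to 78%.

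**Centre.** If centre explains a share R of the variance, the unadjusted SE is about 1/√(1 − R) times the centre-adjusted SE: 1.03 at R = 5% and 1.12 at R = 20%. A simulation used three centres, 10 patients per arm in each, 1:1 allocation balanced within centre, 4,000 runs, and outcomes scaled to unit SD of change. It gave for the unadjusted analysis of change:

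| Centre share (assumed) | Mean model SE | True SD of estimate | Type I error at nominal 5% |
|---|---|---|---|
| 0% (ρ = 0.5) | 0.257 | 0.254 | 4.5% |
| 5% | 0.257 | 0.247–0.252 | 4.5% |
| 20% | 0.258 | 0.226–0.233 | 2.2–3.0% |

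The first row shows that omitting baseline alone does not distort the standard error. The last row shows the conservatism from an omitted stratum. Its exact size varies with the simulation set-up: another three-centre simulation gave 3.7% at a 20% share.

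**The case against.** The strongest reply is that this is a condensed article and that covariate lists belong in an SAP, which is not shown and may name both terms. That limits the criticism. Still, the article does more than stay silent: it commits to a method and makes adjustment optional, and a better method is available from data already collected.

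Other parts of the reply stand:

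- A reader might infer that baseline Hb is ignored. It is not, because it enters through the change score, and subtraction removes additive imbalance. Only covariate adjustment is missing.
- A reader might infer that adjustment is restricted to age and sex. The list is open, and the Discussion also foresees a stratified analysis by Western treatment regimen.
- A reader might infer that the visit-wise contrasts use raw Hb, which would lose much more power at high correlation. The Statistical analyses section speaks of changes, so this reading is not supported.
- Centre as the stratum is the natural reading but is not stated outright. The wording could describe who assigns patients. The same section describes a single list of numbers 1 to 60, and the participants section says randomisation is central. If centre is not the stratum, the argument about conservative standard errors falls for centre.
- If last-observation-carried-forward keeps all 30 per arm in the analysis, unadjusted power is already 90% on the same assumptions, and adjustment takes it to 97%, 94% and 92% at ρ = 0.4, 0.7 and 0.9.

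**Conclusion.** The point holds as a loss of efficiency. The planned Hb analysis has no baseline covariate and no stratum term, and the adjustment it mentions is optional. On SD 7, difference 6, 21 per arm and equal variances, the cost lies between roughly 2 and 13 percentage points of power for ρ from 0.9 down to 0.4. It can be close to nil if Hb is more variable at follow-up than at baseline. The correlation, the variance ratio and the centre share are all assumptions. With little variation between centres, omitting centre hardly matters.

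A reader might go further and infer a biased treatment effect, an inflated false-positive rate, or intervals that are wrong because baseline is left out. The documents support none of these. Intervals that are too wide for the true sampling variation follow only from omitting a stratification factor that predicts Hb, and that error is in the conservative direction.

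**What to change.** State one pre-specified main analysis: Hb, or change in Hb, compared between arms with baseline Hb (continuous) and the randomisation stratum as required terms. Say plainly in the randomisation section what the stratum is; if it is centre, enter the three hospitals as a fixed factor. Move age and sex to a sensitivity analysis. For each continuous secondary outcome (symptom score, iron indices, hepcidin, inflammatory markers), adjust for its own baseline value in the same way.

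The change is a sentence or two of text. It needs no new data and uses about three degrees of freedom: one for baseline and two for three centres.
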